## Abstract

**Background:**

The integrated treatment of first episode psychosis has been shown to improve functionality and negative symptoms in previous studies. In this paper, we describe a study of integrated treatment (individual psychoeducation complementary to pharmacotherapy) versus treatment as usual, comparing results at baseline with those at 6-month re-assessment (at the end of the study) for these patients, and online training of professionals to provide this complementary treatment, with the following objectives: 1) to compare the efficacy of individual psychoeducation as add-on treatment versus treatment as usual in improving psychotic and mood symptoms; 2) to compare adherence to medication, functioning, insight, social response, quality of life, and brain-derived neurotrophic factor, between both groups; and 3) to analyse the efficacy of online training of psychotherapists.

**Methods/design:**

This is a single-blind randomised clinical trial including patients with first episode psychosis from hospitals across Spain, randomly assigned to either a control group with pharmacotherapy and regular sessions with their psychiatrist (treatment as usual) or an intervention group with integrated care including treatment as usual plus a psychoeducational intervention (14 sessions). Training for professionals involved at each participating centre was provided by the coordinating centre (University Hospital of Álava) through video conferences. Patients are evaluated with an extensive battery of tests assessing clinical and sociodemographic characteristics (Positive and Negative Syndrome Scale, State-Trait Anxiety Inventory, Liebowitz Social Anxiety Scale, Hamilton Rating Scale for Depression, Scale to Assess Unawareness of Mental Disorders, Strauss and Carpenter Prognostic Scale, Global Assessment of Functioning Scale, Morisky Green Adherence Scale, Functioning Assessment Short Test, World Health Organization Quality of Life instrument WHOQOL-BREF (an abbreviated version of the WHOQOL-100), and EuroQoL questionnaire), and brain-derived neurotrophic factor levels are measured in peripheral blood at baseline and at 6 months. The statistical analysis, including bivariate analysis, linear and logistic regression models, will be performed using SPSS.

**Discussion:**

This is an innovative study that includes the assessment of an integrated intervention for patients with first episode psychosis provided by professionals who are trained online, potentially making it possible to offer the intervention to more patients.

**Trial registration:**

NCT01783457 clinical trials.gov. Date of registration in primary registry 23 January 2013.

## Background

The definitions of the words psychotic and psychosis [1] refer to the occurrence of delusions and hallucinations, without specifying their nature in terms of the underlying disease or mental illness. The incidence of psychosis falls with age and is twice as high in men as in women [2]. Around 20% of patients with a first psychotic episode will have no further episodes [3]. This means, however, that symptoms do recur in the great majority of patients.

A recent meta-analysis indicated that the factors that best predict the occurrence of relapses are failure to adhere to treatment, persistent substance abuse disorders, negative comments from caregivers and poor premorbid adjustment [4]. With regards to treatment, previous studies have demonstrated that individuals who receive early intervention including guidance on how to improve their adherence to treatment, insight into their illness and self-management and how to minimise substance use have a better course and, hence, these factors are associated with a better prognosis [5–10]. Indeed, it has been observed that delays in the treatment of psychosis tend to be associated with slower recovery, greater suffering, a higher level of comorbidity and greater deterioration in family and social relationships [11]. Further, the critical period of the disease (the first 5 years) is a relatively reliable indicator of the long-term course of the disease [12, 13]. Overall, it seems that interventions carried out as early as possible improve prognosis and quality of life in these patients.

Regarding the types of treatment for patients with first episode psychosis, a review concluded that early psychosocial interventions adjunctive to pharmacotherapy may contribute to patient symptomatic and functional recovery [14]. Various types of treatment have shown efficacy in these patients. For instance, some authors recommend cognitive behavioural therapy during the acute stage of the disease or during remission [15]. However, systematic reviews have found that integrated treatment (including biological, psychological and social elements) is the approach that most significantly reduces the rates of transition to psychosis and negative symptomatology compared to treatment as usual. Further, integrated treatment has proven efficacy in various areas, being associated with less psychotic symptomatology at 2 years follow-up, fewer negative symptoms, better global functioning, lower rates of substance abuse, lower doses of the second-generation antipsychotic medications and fewer days of hospitalization [16–19]. A clinical trial also found that this type of treatment produces good results in the first stages [20]. Nevertheless, there is a need for more randomised controlled clinical trials to assess the effectiveness of these interventions [14].

On the other hand, it has been shown that disciplines, such as cognitive behavioural therapy, that have a shortage of formally trained clinicians could benefit from online learning [21]. In particular, a European project has demonstrated the effectiveness of teaching integrated treatment through the web [22]. New forms of transmission of these skills could be an important way for clinicians to gain access to specialist knowledge, and facilitate access to training for more clinicians.

This study hopes to shed light on these issues, with an improved methodology; it is a pragmatic trial - that is, there is no selection of a specific type of patients - and the aim is to assess the effectiveness of individual psychoeducation as well as the remote training of therapists.

The primary objective of this study is to assess the efficacy of a psychoeducation programme in improving the symptomatology of patients; namely the positive, negative, and general symptoms of psychosis, measured using the Positive and Negative Syndrome Scale (PANSS), State-Trait Anxiety Inventory (STAI), and Hamilton Rating Scale for Depression (HRSD).

The secondary outcomes of interest are patient functioning (measured using the Strauss and Carpenter Prognostic Scale, Global Assessment of Functioning (GAF) scale, Functioning Assessment Short Test (FAST)), adherence (Morisky Green Medication Adherence Scale), insight (Scale to Assess Unawareness of Mental Disorders (SUMD)), social response (Liebowitz Social Anxiety Scale (LSAS)), quality of life (World Health Organization Quality of Life instrument WHOQOL-BREF (an abbreviated version of the WHOQOL-100) and the EuroQoL questionnaire), and brain-derived neurotrophic factor (BDNF) level.

We also want to analyse the efficacy of online training of psychotherapists.

In this paper, we describe in detail the study design, patient selection and evaluation, the programme of psychoeducation under study, and training of professionals. It is an intervention study of integrated treatment for patients with first episode psychosis, with the innovation that the participating therapists will receive remote training.

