## Methods

### Design

We registered this single-blind randomised clinical trial in 2013 (identifier NCT01783457). Patients with a first episode of psychosis between 2010 and 2014 are to be included and randomly assigned to one of two treatment groups: the control group, receiving pharmacotherapy together with regular sessions with a psychiatrist (treatment as usual), and the intervention group receiving integrated treatment, namely treatment as usual plus a psychoeducational intervention (12 main sessions and 2 booster sessions). A first psychotic episode was defined as the first time a patient displayed positive psychotic symptoms of delusions and/or hallucinations.

We are recruiting patients from five psychiatric centres (University Hospital of Álava, Clinic Hospital of Barcelona, Clinical Foundation of Valencia, University Hospital of Bellvitge, and University of Valencia) that agreed to take part in the e-learning project. In all centres, the clinicians recruit subjects who show psychotic symptoms for the first time, and who meet the inclusion criteria (listed below). To obtain 90% power to detect differences in the means at the 5% level of significance, we have estimated that we need to enrol 130 patients in each group (study group and controls) (alpha = 0.05; beta = 0.10; n = 260).

The treatment is being supervised by one clinician (PV) trained by a highly experienced clinician at the University Hospital of Álava (SB), while the evaluations in all centres are conducted by other clinicians blind to patient allocation.

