#### Symptomatology

Participants’ symptoms are assessed using the PANSS [23]. This instrument is composed of 30 items that assess positive and negative symptoms as well as the general psychopathology of the disorder. Each item is measured using a 7-point Likert scale reflecting the severity of symptoms, from 1 (none at all) to 7 (extreme symptoms). This scale has been validated in Castilian Spanish [24].

Trait and state anxiety are measured using the STAI [25]. This instrument has two parts: one assesses the anxiety experienced by patients in the previous week (state) using 20 items with four response options; while other part, also composed of 20 items with four response options, assesses their usual reactions to certain situations (trait anxiety). The STAI was adapted from the version described in a Spanish paper by Bermúdez in 1978 [26]; across all these items the mean and the reliability (Cronbach’s alpha and test-retest correlation) are similar to those of the original version [27].

Patients’ social anxiety is assessed using the LSAS [28], and its psychometric properties have been found to be satisfactory in the Spanish population [29]. Lastly, mood is evaluated using the HRSD [30], which has also been validated in Castilian Spanish [31].

In addition, in relation to symptoms, we record information on the number of relapses and hospital admissions (psychotic episodes) and the dates on which they occur for 2 years follow-up, the psychopharmacotherapy administered, family history of mental health problems, and record of substance use both before and after the intervention.

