### Data processing

We used Gridsam, the central database of the Spanish research network for mental health (CIBERSAM). This database facilitates the merging of large amounts of data and access to the records.

Comparisons of baseline characteristics of the sample will be made with χ^2^-tests for categorical variables and the Student’s *t*-test or Mann Whitney U test for quantitative variables. Within-group changes in symptomatology and functioning during treatment will be examined using paired *t*-tests.

Univariate analyses of covariance will be conducted to investigate differences between groups. For this, the independent variable is the group assignment (integrated treatment versus control) and the dependent variable is the respective clinical or functional outcome score post-treatment. Recurrence-free curve analysis will be performed using Kaplan–Meyer survival analysis to analyse the relapses in the groups during the follow-up. This analysis will be performed on an intention-to-treat basis, with patients being analysed in the treatment group to which they were randomised.

In addition, a logistic regression model will be used to analyse the association between clinical variables. Finally, we will also build a logistic regression model to explore factors associated with changes in variables during follow-up.

The outcomes will be reported with 95% confidence intervals. All data will be analysed using SPSS (version 21.0; IBM Corp. Released 2012. IBM SPSS Statistics for Windows, Version 21.0. Armonk, NY: IBM Corp.

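### The primary objective covers five or six symptom scores, but no deciding score or success rule is named, and the sample size uses one unsplit 5% alpha for an unnamed mean

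*Protocol article*

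**What the plan says.** - **Primary objective (Background).** The aim is better symptomatology, "namely the positive, negative, and general symptoms of psychosis, measured using the Positive and Negative Syndrome Scale (PANSS), State-Trait Anxiety Inventory (STAI"). A depression scale, the HRSD, completes the list. All of these stand at the same level. The secondary outcomes are listed separately in the next paragraphs. The abstract's first objective is no narrower: "improving psychotic and mood symptoms".
- **Symptomatology section.** On the STAI: "This instrument has two parts: one assesses the anxiety experienced by patients in the previous week (state"), and the other part covers trait anxiety. The article does not say whether the STAI enters the analysis as one score or two.
- **Design, sample size.** "To obtain 90% power to detect differences in the means at the 5% level of significance", the authors estimate that "we need to enrol 130 patients in each group (study group and controls"), with "alpha = 0.05; beta = 0.10; n = 260". The section does not say which variable, what difference or what SD this refers to.
- **Data processing.** Between-group differences are examined by univariate analyses of covariance in which "the dependent variable is the respective clinical or functional outcome score post-treatment". That means one test per score. Results are to carry 95% confidence intervals.

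The article states no ranking among the primary scores and no rule for how many must be significant.

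**The concern.** The objective, the sample size and the between-group analysis are all stated, and they do not fit together. The objective has several scores, the analysis tests each one, and the sample size allows for one test at an undivided 5%. A reader of the eventual results could not tell from this article which finding answers the primary question.

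Two things are at stake. If one favourable score is enough, the error rate of the primary claim exceeds its nominal level, and the score that carries the claim can be chosen after the results are seen. If every score must be significant, the 90% power does not apply. The Discussion says the results might lead to the programme's adoption in routine practice, so the meaning of a positive result should be fixed in advance.

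**Working it through.** **Inputs from the article.** 130 per group; alpha 0.05; power 90%; PANSS positive, negative and general, STAI and HRSD as primary; one ANCOVA per score.

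**Assumptions of this check.** Two-sided tests (in line with the 95% intervals); each score tested at 5%; k = 5 scores (STAI once) or k = 6 (state and trait); normal test statistics with a common correlation ρ from 0 to 0.9. The article gives no correlations.

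**1. The article's own figure.** The 130 per group cannot be reproduced, because no difference or SD is given. It can only be solved backwards:

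d = (1.960 + 1.282) × √(2/130) = 3.2415 × 0.1240 = 0.402 SD (0.404 with the noncentral t).

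The standardised test statistic then has mean δ = 0.402 × √(130/2) = 3.24.

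**2. If any one significant score counts.** With all nulls true and independent tests:

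- Six scores, either direction: 1 − 0.95⁶ = 0.265. Five scores: 1 − 0.95⁵ = 0.226.
- Six scores, benefit only: 1 − 0.975⁶ = 0.141. Five scores: 1 − 0.975⁵ = 0.119.

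For ρ > 0, with c = 1.960:

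1 − ∫ [Φ((c − √ρ x)/√(1−ρ)) − Φ((−c − √ρ x)/√(1−ρ))]ᵏ φ(x) dx

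The second Φ term is dropped when only benefit is counted.

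| ρ | 6 scores, either direction | 5 scores, either direction | 6 scores, benefit only | 5 scores, benefit only |
|---|---|---|---|---|
| 0 | 26.5% | 22.6% | 14.1% | 11.9% |
| 0.5 | 20.7% | 18.3% | 10.4% | 9.2% |
| 0.7 | 16.4% | 14.8% | 8.2% | 7.4% |
| 0.9 | 10.8% | 10.2% | 5.4% | 5.1% |

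The single-test reference is 5% for either direction and 2.5% for benefit. Counting only the three instruments, one score each, the either-direction figure runs from 14.3% (ρ = 0) to 8.4% (ρ = 0.9).

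**3. If all scores must be significant.** Take the 0.402 SD effect as present on every score, so each test has 90% power:

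∫ [1 − Φ((c − δ − √ρ x)/√(1−ρ))]ᵏ φ(x) dx

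- Six scores: 0.9⁶ = 53% at ρ = 0, 68% at 0.5, 74% at 0.7, 82% at 0.9.
- Five scores: 0.9⁵ = 59% at ρ = 0, 76% at 0.7, 83% at 0.9.

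**4. What control would cost.** The strictest Holm step with six scores is 0.05/6 = 0.0083, critical value 2.638.

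- Power for one given score at that step: Φ(3.2415 − 2.638) = Φ(0.603) = 73% (72% with the noncentral t).
- Sample size for 90% power per score at that level: 2 × (2.638 + 1.282)² / 0.402² ≈ 190.1, so 191 per group.
- Power for at least one win at that level, with 0.402 SD on all six scores (integral in step 2 with c = 2.638 and means shifted by δ): about 96% at ρ = 0.5 and 92% at ρ = 0.7.

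**The case against.** The strongest objection is that this is a condensed article. A multiplicity procedure can properly sit in a statistical analysis plan or full protocol that is not shown, so its absence here proves nothing. That stands: a missing adjustment method is not the finding. It does not dispose of the point, because which outcome decides the trial, and which outcome the sample size refers to, are protocol-level choices. The article makes statements on both that do not agree.

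A reader might go further and infer that the trial has six primary tests at 5% with no hierarchy or correction, and hence a false-claim rate of 16–26%. The article does not support that as fact:

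- It never says six; counting the STAI once gives five.
- It states no rule that one significant score is enough.
- A floor of 16% needs a correlation of at most about 0.7, for which the article gives no source.
- The figure counts differences against the intervention as well as for it.

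A reader might also take the 72% at 0.05/6 as the power of the primary claim after correction. It is the power for one given score. If any adjusted win sufficed, power would be well above 90% at correlations of 0.5 to 0.7, under the assumption of an equal effect on all scores.

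Finally, a reader might conclude that PANSS total should be the primary outcome, or that trait anxiety does not belong in the set. The primary objective names the three PANSS domains and never a total. The article's description of trait anxiety does not show that it cannot change in 6 months. Those would be preferences, not corrections.

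**Conclusion.** The concern holds in a conditional form. The primary objective spans five or six scores, each with its own test. One unsplit alpha and one sample size are given for an unnamed comparison, and no deciding score or success rule is stated.

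The error figures illustrate an any-one-wins reading and depend on the assumed correlations. The power figures illustrate an all-must-win reading; they rest on the back-solved effect being equal on every score, and would be lower if it were smaller on some. Neither set is a property the article declares. The conclusion does not depend on guessing the intended rule: under the first reading the nominal 5% fails, and under the second the nominal 90% fails. This should be settled before analysis, because the main conclusion of the trial is otherwise undefined.

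**What to change.** The article reports that recruitment is not complete, so the choice can still be made before the results are known. Either route works:

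1. **One primary outcome.** Name one of the listed scores, at the sponsor's choice, as the single primary outcome at 6 months. State the difference and SD behind the 130 per group for that score, and treat the other scores as secondary. Alpha stays at 5%. The 130 per group is unchanged if it was in fact calculated for that score.
2. **All scores primary.** State whether the STAI counts as one score or two, apply Holm across the set at an overall two-sided 5%, and say what constitutes success. Restate the power accordingly: about 72% per score at the strictest step with six scores, or about 191 per group for 90% per score, both at the assumed 0.40 SD.

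The cost is mainly wording in the protocol and analysis plan. Under the first route, an isolated significant result on another score no longer counts as primary success. Under the second, an unadjusted p below 0.05 on one score is not enough by itself, and the stated power per score is lower unless the sample grows.

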#### Randomisation

All individuals with first episode psychosis that meet the selection criteria are randomised with random allocation software. For this purpose, all the groups from the participating centres send the initials of each patient recruited to researchers at the coordinating centre who specify the allocation of the patient (to the control or intervention group); the person in charge of the assessments is blind to this process.

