### Online training

The coordinating group carried out the training of the therapists in the participating centres, via teleconferencing (WebEx Training Center). The course consisted of 12 modules and 2 booster sessions, corresponding to the 14 sessions of the psychoeducational programme, and all the participating groups received the same theoretical content. Once all the materials had been provided and explained, participating groups were asked to perform a task with certain objectives, each group having to complete this before starting the following module.

In addition, all the therapists participating in the online training had to prepare a case study with theoretical and practical elements and correctly complete a task under the supervision of a psychotherapist with extensive experience in the field of psychoeducation, before they themselves carried out the psychoeducational intervention with the patients. As well as providing written support material, we attempted to ensure the correct integration of knowledge presented by giving feedback, correcting answers participants gave during sessions, and correcting hypothetical cases presented. At the end of each module, all the therapists were required to complete a form recording the learning objectives covered in the module and testing their knowledge of theoretical and practical aspects of the psychoeducation programme.

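### Objective 3 claims to analyse the efficacy of online therapist training, but the design has only one training condition and can support no more than a descriptive statement

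*Protocol article*

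**What the plan says.** The training aim appears three times in the protocol article:

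- Abstract, Background, as a numbered objective: "3) to analyse the efficacy of online training of psychotherapists".
- Background, where it shares the study's aim with the patient question: "the aim is to assess the effectiveness of individual psychoeducation as well as the remote training of therapists".
- End of the Background, after the secondary outcomes: "We also want to analyse the efficacy of online training of psychotherapists". The patient outcomes just before it each come with an instrument. This sentence comes with none.

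The design features that bear on it are these:

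- **Centres (Design).** Patients come from five centres, all of them centres "that agreed to take part in the e-learning project".
- **Training (Online training).** The coordinating group taught the course by teleconference, and "all the participating groups received the same theoretical content". The section is written in the past tense.
- **Allocation (Randomisation).** The unit is the patient: "All individuals with first episode psychosis that meet the selection criteria are randomised with random allocation software".
- **Control arm (Design; Treatment as usual).** Drug treatment and regular psychiatrist appointments, with no psychoeducation.
- **Therapist data (Online training).** A task for each group at each module, a case study and a supervised task before treating patients, and a knowledge form from every therapist at the end of each module.

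**The concern.** A claim that training is efficacious needs something to compare it with: the same programme delivered by therapists trained another way, or not trained. The article describes no such group among therapists, centres or patients.

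At stake is what the trial may conclude. The article presents remote training as its innovation. If the patient result is favourable, it will be natural to report that online training works as well. If the result is null, it will be natural to ask whether the programme or the training failed. The design supports an answer in neither case.

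**Working it through.** The question is one of identification, and the article gives no figure for this objective, so there is none to reproduce. Its only sample size, 130 patients per group (260 in total) for 90% power at the 5% level, belongs to the patient comparison.

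**Step 1. Count the conditions.**

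| Element | What the article provides | Number |
|---|---|---|
| Training conditions | Same content for all groups | 1 |
| Centres outside the e-learning project | None of the five | 0 |
| Therapists or centres allocated to another form of training | Only patients are allocated | 0 |
| Patient arms receiving psychoeducation | Intervention arm only | 1 |

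**Step 2. Write down what the patient comparison estimates.** Let Δ be the difference in mean outcome between the arms. Let P be the effect the programme would have if delivered by therapists prepared in some reference way (conventional training, or none). Let T be the change in that effect due to online training instead of the reference. Then

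Δ = P + T.

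The trial estimates Δ. Objective 3 concerns T. To obtain T one must know P, which requires patients treated by therapists prepared in the reference way. Step 1 shows that there are none. That leaves one equation with two unknowns.

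**Step 3. Read the possible results.**

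- *Δ favourable.* Every value of T fits, with P = Δ − T. T = 0 (training mode irrelevant) fits, as does a T that weakened a stronger programme.
- *Δ = 0.* P = 0 with T = 0 fits (an ineffective programme). So does P > 0 with T = −P (an effective programme undone by poor training).

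A larger trial narrows the interval around Δ and leaves T undetermined. This is therefore not a matter of power.

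**Step 4. Ask what the therapist data can add.** The knowledge form is completed after each module, by therapists who all took the same course. It gives the level of knowledge attained. The tasks and case study give completion. A pre-training score, if the full protocol has one, would add the change in knowledge over the course. That would still be an uncontrolled change in knowledge, with no comparison against another way of training and no link to patient benefit.

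**The case against.** The strongest reply is that this is a condensed article. The full protocol or statistical analysis plan may say how the knowledge forms are scored, whether there was a pre-training test, and how the results are summarised. That stands: the silence of the Data processing section on therapist data is not itself a fault. It does not rescue the objective, because no analysis plan can supply a comparator that the published design excludes, and the training is reported as already given.

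A second reply is that the training aim is minor, and that the Discussion claims wider access and lower cost for online training, not efficacy. This also has force, and it limits the weight of the point. The abstract nevertheless numbers it as an objective, and the Background makes it part of the aim.

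Three stronger readings are tempting, and the document does not support them:

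- *That no therapist data exist.* They do. The sound statement is that, without a comparator, they cannot show efficacy.
- *That therapist knowledge is at its ceiling because progress was gated.* The rule between modules is "each group having to complete this before starting the following module". It applies to groups and asks for completion. Correct performance is required at a separate step, before therapists treat patients. No pass mark is given for the knowledge form.
- *That comparing the coordinating centre with the other four would test the training.* The coordinating hospital is listed among the centres in the e-learning project, and the article does not say how its own therapists were trained. The comparison would also be non-randomised and confounded with everything else that differs between centres.

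**Conclusion.** The point holds. As worded, objective 3 cannot be met: with one training condition, randomisation of patients only and a control arm without psychoeducation, the effect of the training mode cannot be separated from that of the programme. A conclusion on the efficacy of training would be unsupported whichever way the patient result falls.

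The conclusion rests only on design features that the article states. It needs no assumed effect size or recruitment split, and its size is not a number: the information on the training effect is nil, not merely imprecise.

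The weight is moderate. A reader might infer that the trial's main result is compromised, but it is not. The randomised comparison of psychoeducation plus usual treatment with usual treatment alone, its sample size and its patient analyses are untouched.

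**What to change.** Restate objective 3 as descriptive: to describe the feasibility of training therapists remotely and the knowledge they attained. Name the measures from what is already collected and report them by centre: modules completed, knowledge-form results, and therapists completing the training.

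Remove efficacy and effectiveness of training from the objectives in the Abstract and Background, and keep both words out of the conclusions where they refer to training. Do not add a comparison of the coordinating centre with the other centres as a substitute.

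The change is a rewording plus one descriptive table from data already collected. It needs no new patients, therapists or measurements. The cost is a weaker headline: the trial could say that remote training was delivered and what therapists learned, but not that it was efficacious.
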